**EFFECT OF NEUROMUSCULAR TRAINING ON FUNCTIONAL CAPACITIES IN PATIENTS WITH ACUTE CORONARY SYNDROME**

INTRODUCTION

Acute myocardial infarction (AMI) is defined as a clinical picture produced by ischemia and subsequent death of a more or less extensive portion of the myocardium, as a consequence of the obstruction of a coronary artery. When flow obstruction occurs, the blood supply to the myocardial tissue is suppressed, producing an oxygen deficit that, if maintained over time, produces non-reversible necrosis of the affected myocardial area^1,2^.

In the past decade, ischemic heart disease caused up to 29% of deaths in industrialized countries, becoming the main cause of death, a figure that will remain in 2020 according to the latest projections^3^. However, a decrease in mortality from ischemic heart disease has been observed, related to a lower incidence and to the improvements introduced in recent years both in the acute phase treatment of acute myocardial infarction and in primary prevention ^4,5^.

The clinical manifestations of heart disease are extensive, with chest pain as the main sign, presenting with strong intensity and without yielding to rest. The radiation of this pain can be variable (interscapular, mandibular, cervical, upper limbs, etc.) and can be accompanied by nonspecific signs such as dyspnea, sweating and dizziness, among others^1,6^.

In addition to the acute symptoms of the disease, after AMI patients have to learn to live with the consequences of the disease and its treatment, which can lead to a deterioration in health-related quality of life (HRQoL) ^7, 8^. There is no consensus on the concept of HRQL, but what the different authors agree on is that it is a complex and multidimensional concept that acquires great importance when evaluating the impact of a disease or health problem, in which case we are talking about HRQL. This concept encompasses aspects such as physical symptoms; cognitive function and psychological well-being; performance or role and social welfare; the global state of health; the perception of care and personal constructs^8,9^.

Sexual activity is an aspect that affects HRQoL in patients with acute myocardial infarction (AMI) and their spouses^10,11^. Both the usual treatment of patients, as well as cardiovascular adaptations during sexual intercourse, can aggravate the symptoms of heart disease by increasing oxygen consumption^12-14^. This energy consumption during sexual intercourse in the usual position and with the usual partner is equivalent to 3-4 METs (Metabolic Equivalent or Metabolic Equivalent of Task), a MET being the oxygen consumption per minute of a person at rest in relation to their body weight. Although sexual activity is a risk factor for patients who have suffered AMI, patients who can exercise whose energy consumption is equivalent to or greater than 5 METS, are in a position to resume sexual activity^12,15^.

The importance of a heart-healthy lifestyle, which includes physical exercise, has been described and evidenced in both adult and pediatric populations^16^. The implementation of comprehensive evaluation programs of cardiopulmonary function and the response to physical activity, as well as the design of cardiac rehabilitation based on this evaluation, can favor the quality of life of patients with heart disease after acute myocardial infarction, in addition to be very useful for evaluating the clinical status and prognosis of the patient.

Cardiac rehabilitation programs (CRP) are multifactorial action systems recommended by the World Health Organization since the 1960s. There is scientific evidence that these programs not only favor the control of cardiovascular risk factors (CVRF), but also act on quality of life, favoring work reintegration and reducing the morbidity and mortality of patients, in addition to demonstrating in a way its viability has been unequivocal as its effectiveness has been verified at the cost-benefit level^17-19^.

Contraindications to performing CRPs have been reduced in recent years thanks to a better understanding of the results and dangers inherent in exercising. Those that could be considered as absolute are reduced to dissecting aortic aneurysms and severe obstruction of the left ventricular outflow tract without surgical indication^1,4^.

The CRPs are divided into three phases. Phase I includes the hospital stay, which can also occur with a patient in the phase before and after cardiovascular surgery. This phase includes early mobilization and respiratory exercises, as well as control of CVRF and psychological action. Phase II lasts approximately two months and begins from the moment of hospital discharge. The clinical data and results of the examinations (such as echocardiography, ergometry, nuclear medicine, etc.) allow patients to be classified at different risk levels. This phase consists of 20-24 sessions with two or three face-to-face sessions in the rehab center, including a 10-minute warm-up period, a 30-40-minute aerobic workout, and a 10-minute recovery phase. The intensity of the exercise is determined according to the data of a stress test, and is increased as a function of the chronotropic and tension response of the patient to the training, in addition to her subjective perception of effort. Phase III is maintained for the rest of the patient's life. It is performed out-of-hospital and, after a written report from the cardiologist, the cardiovascular patient continues with the established physical exercise guidelines, control of CVRF, and socio-occupational and psychological aspects in centers equipped with the material and human equipment necessary for the continuation of his rehabilitation^1,4,16,18,20^.

In recent years, the study of movement dysfunction and its influence on the efficiency of sports gesture performance, especially of the lower limb, has undergone considerable development. From the studies by Sahrmann et al.^21-25^, to the most recent ones carried out by Comerford et al.^26,27^, the importance of neuromuscular control to improve movement quality and prevent injuries derived from this lack of control has been evidenced. This type of training focuses on several key elements such as core stability, performing them in a functional posture, lower limb strength work, and functional exercises^28^.

Despite the fact that the bulk of the evidence on the benefit of this type of work is in the world of sport due to its importance in preventing injuries and improving control and proprioception of the joint segments, other studies are testing the effectiveness of this work for other populations^29,30^. For example, the GLA: DTM program, a neuromuscular training program run by physiotherapists throughout Denmark is being carried out to improve the symptoms caused by hip osteoarthritis in adult and elderly populations. However, its authors point out the need to study the potential of this type of work not only in pathologies of neuromuscular etiology, but also in other chronic or supervening diseases and in the ability to improve the general condition of the patient^31^. For this reason, we propose this study to know the possible benefits of this work compared to a traditional force protocol.

OBJECTIVES

The general objective of the study is based on verifying whether neuromuscular training is more effective compared to the classic strength training of Cardiac Rehabilitation Programs to improve the functional capacities in patients after acute myocardial infarction.

The specific objectives of this project are:

- Analyze the effect of the intervention on functional parameters of lower limbs

- Determine the effect of the program on variables of strength of respiratory and peripheral muscles

- Analyze the impact of a cardiac rehabilitation program on the quality of life of patients who have suffered an AMI

- Determine the variables that influence the sexual activity of patients after AMI and the impact on their quality of life

METHODS

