**Design**

The study is presented as a randomized controlled trial, an experimental scientific procedure characterized by the random distribution of the members of a suitable population group into an intervention group and a control group, comparing a specific impact between the groups after a period established in advance.

Its design is a pre-post, based on the measurement and comparison of the variables to be studied before and after the exposure of the participants to the experimental intervention.

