**Intervention: training program**

Phase II of the cardiac rehabilitation program will be based on the F.I.T.T.^32,33^ model, where the main parameters are the frequency of training, the intensity of the exercise, the duration of the sessions / complete program, and the type of exercise proposed:

- FREQUENCY. 2 sessions per week in a cardiac rehabilitation gym. In addition, the work will be complemented with a pattern of home exercise.

- INTENSITY. Intensity based on maximum oxygen consumption (VO2) and maximum heart rate (HR), calculated based on the ergospirometric tests performed. The Training HR (FCE) will be that given by the ventilatory thresholds obtained in the Wasserman curves.

- TIME. The sessions will last approximately 60 minutes (approximately 40 minutes of them correspond to the training phase). The program will include a total of 20 sessions (2 sessions a week for approximately 10 weeks).

- TYPE. The type of work indicated in cardiac rehabilitation programs in the aerobic phase will be the continuous and interval modality, which will be established depending on the risk stratification of the patient.

All patients will be monitored through a heart rate and O2 saturation recognition device. In addition, the patient's subjective perception of effort will be monitored at all times using the modified Borg Scale, both at the level of dyspnea and lower limb fatigue.

The sessions will be structured as follows:

Warm-up Phase (10 minutes):

- Respiratory exercises: Diaphragm + respiratory muscles training

- Low-intensity walking

Training Phase (40 minutes):

- Aerobic Exercise Phase on treadmill / cycle ergometer (20 minutes)

- Strength Exercise Phase (20 minutes) (Annex II)

Cooldown Phase (10 minutes):

- Low-intensity walking

- Stretching

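### The third specific objective asks for the effect of cardiac rehabilitation on quality of life, which a trial with rehabilitation in both arms cannot estimate

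*Protocol*

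**What the plan says.** All places are in the protocol.

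- **Objectives, general.** The trial asks whether "neuromuscular training is more effective compared to the classic strength training of Cardiac Rehabilitation Programs". This is a contrast between two forms of strength training.
- **Objectives, third specific.** The aim is to "Analyze the impact of a cardiac rehabilitation program on the quality of life of patients who have suffered an AMI". The exposure named is rehabilitation as a whole.
- **Objectives, second specific.** The aim is to "Determine the effect of the program on variables of strength of respiratory and peripheral muscles". Which program is meant is not said.
- **Intervention: training program.** One Phase II programme is described: "The program will include a total of 20 sessions (2 sessions a week for approximately 10 weeks"). Every session has the same warm-up, aerobic phase and cool-down, and a home exercise pattern is added. The warm-up includes "Respiratory exercises: Diaphragm + respiratory muscles training". The only component that points to alternative versions is "Strength Exercise Phase (20 minutes) (Annex II").
- **Annex II.** It gives a classic and a neuromuscular version of that strength block.
- **Design.** The trial is randomised and compares groups. The section then adds: "Its design is a pre-post, based on the measurement and comparison of the variables to be studied before and after the exposure" to the experimental intervention.
- **Statistical analysis.** A split-plot model is planned, with time (PRE, POST, POST1) within subjects and group (Intervention, Control) between subjects. The section does not say which model term answers which objective.

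**The concern.** An objective should name an effect that the design can estimate. The third specific objective names the effect of rehabilitation, but every patient receives rehabilitation. The randomised comparison therefore says nothing about that effect, and the only quantity left to answer the objective is the before-after change.

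After an acute coronary event, quality of life may improve for reasons unrelated to the programme, such as spontaneous recovery, drug treatment, familiarity with the questionnaire and regression to the mean. An improvement over time could then be taken as evidence that rehabilitation improved quality of life, a causal conclusion with no control group behind it.

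**Working it through.** **Step 1. What the arms share.** A session has a 10-minute warm-up, a 40-minute training phase and a 10-minute cool-down: 10 + 40 + 10 = 60 minutes. The training phase is 20 minutes aerobic plus 20 minutes strength. Only the strength block has two versions, so 60 − 20 = 40 minutes per session are described once for everybody. That controls receive the classic block follows from reading the general objective, the intervention section and Annex II together. It is not stated in a single sentence.

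**Step 2. What can be identified.** Take effects as additive and write the mean change in EQ-5D from PRE to POST as the sum of:

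- R: change that would occur without any rehabilitation (recovery, medical treatment, retest learning, regression to the mean);
- S: effect of the shared programme components;
- C or N: effect of the classic or the neuromuscular block.

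Then:

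- change in the control arm = R + S + C
- change in the intervention arm = R + S + N
- difference between arms (group-by-time) = N − C
- pooled change (time effect, equal arms) = R + S + (N + C)/2

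The third specific objective asks for S + C, S + N or an average of the two. R cancels from the between-arm difference, but so does S. In the pooled change S remains, but so does R. With no arm in which S, C and N are all absent, R cannot be separated out. This conclusion needs no numerical assumption.

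**Step 3. How large the confusion could be.** The protocol states no sample size, SD or effect, so there is no figure to reproduce. The following rests on assumed values.

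*Single case.* Assume 60 patients in total, an SD of 15 for the change in the EQ-5D visual analogue scale, and a natural recovery of 5 points with zero programme effect.

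- SE = 15/√60 = 1.94
- 5/1.94 = 2.58
- P(Z > 1.96 − 2.58) = P(Z > −0.62) = 0.73

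*Range.* Simulation with 4000 runs per setting, two arms, two time points, pre-post correlation 0.6 (SD of change = √(2 × (1 − 0.6)) = 0.89 SD) and two-sided α = 0.05. Programme effect and arm difference are both zero, and a natural recovery of d SD is common to both arms.

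| n per arm | d (SD) | time effect significant | group-by-time significant |
| --- | --- | --- | --- |
| 20 | 0.2 | 27% | 4.3% |
| 20 | 0.3 | 54% | 5.6% |
| 20 | 0.5 | 92% | 5.3% |
| 30 | 0.2 | 41% | 4.9% |
| 30 | 0.3 | 73% | 4.7% |
| 30 | 0.5 | 99% | 4.3% |
| 50 | 0.2 | 61% | 5.1% |
| 50 | 0.3 | 92% | 5.0% |
| 50 | 0.5 | about 100% | 5.2% |

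The group-by-time term keeps its nominal error rate because recovery common to both arms cancels. The time effect does not, because it tests whether anything changed, whatever the cause. The planned model has three time points, so the table illustrates the mechanism and does not predict this trial's results.

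**The case against.** The strongest reply is that the protocol already plans the right comparison. The Design section describes a randomised trial that compares impact between groups, so *impact* in the third objective could be read in the same sense. The sentence on pre-post measurement refers to the experimental intervention, and the statistical section sets Intervention against Control. Assigning model terms to objectives may also be left to a statistical analysis plan that is not at hand. What stands of this is that the analysis is suitable for a between-arm question. It does not rescue the third objective, whose exposure is a rehabilitation programme rather than a type of strength training. No analysis plan can supply the missing comparator.

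Two stronger readings are tempting, and the document does not support them.

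- **That the protocol intends to present the time effect as programme benefit.** It does not say so. Time is an ordinary factor of a split-plot model. Misreading it is a risk that the wording leaves open and not a stated plan.
- **That the second specific objective fails in the same way.** The protocol uses *program* both for the whole set of 20 sessions and, at the end of the introduction, for neuromuscular training. Under the general objective the word can reasonably mean the latter, so the objective is ambiguous but not unanswerable. Peripheral strength is a direct target of the randomised block. PIM and PEM can also be compared between arms, although a difference is less likely because the respiratory exercises appear to be common to both. That they are common is an inference from a single description not split by arm.

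It is also fair to say that the percentages show only that a non-zero mean change can be detected, which holds for any before-after measure.

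**Conclusion.** The point holds for the third specific objective. As worded, it asks for an effect that the design cannot estimate, and only the uncontrolled change over time could address it. This rests on the inference that controls receive the classic block within the same Phase II programme. The general objective, the intervention section and Annex II all agree with that.

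The severity is low. This is one secondary objective. The general objective is a clear randomised contrast and is unaffected, and no planned test or procedure is wrong because of it. The 27% to about 100% range depends on assumed sample size, recovery and correlation and should not be quoted as a property of this trial. The identification argument does not depend on it. The second specific objective needs a clarification only.

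**What to change.** 1. Reword the third specific objective as the randomised contrast, for example: *to compare neuromuscular with classic strength training, each given within Phase II rehabilitation, on quality of life measured by EQ-5D.* State that the group-by-time term of the planned model answers it.
2. Add one sentence to the statistical section: within-arm and pooled pre-post changes are descriptive and will not be interpreted as an effect of cardiac rehabilitation.
3. In the second specific objective, say that *the program* means neuromuscular versus classic strength training. If the respiratory exercises are indeed the same in both arms, say so, so that a small or absent difference in PIM and PEM is read correctly.

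The cost is a few sentences. No procedure, measurement or analysis changes. What is given up is a claim about rehabilitation itself, which this design could not support.

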**Design**

The study is presented as a randomized controlled trial, an experimental scientific procedure characterized by the random distribution of the members of a suitable population group into an intervention group and a control group, comparing a specific impact between the groups after a period established in advance.

Its design is a pre-post, based on the measurement and comparison of the variables to be studied before and after the exposure of the participants to the experimental intervention.

**Participants**

Participants will be selected based on the following criteria:

Inclusion criteria:

• Subjects diagnosed with acute coronary syndrome with or without ST segment elevation (NSTEACS / NSTEACS), with a Low or Medium risk stratification according to the stress tests performed by the cardiology service of the IMED Valencia Hospital.

• Medical prescription.

• Consent signed by the patient (Annex I).

Exclusion criteria:

• Pathologies that contraindicate exercise: acute inflammatory cardiac disease, severe or moderate LV or RV dysfunction, decompensated HF, serious arrhythmias documented in ICD, significant coronary artery disease, HTN> 40mmHg or requiring treatment with vasodilators, gradient aortic stenosis resting systolic> 50mmHg, pulmonary stenosis with resting systolic gradient <50mmHg, systemic hypertension> 95% percentile, baseline O2 Sat <90%, severe AV valve failure, severe acute kidney disease, acute hepatitis and active infection.

• Alterations in ergospirometry: severe exercise-induced arrhythmias, ST depression with effort, exaggerated hypertensive response, hypotension on exertion and chest pain.

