**Outcome measures:**

Sociodemographic variables: age, sex, educational level, type of work, marital status, time spent with the partner.

Dependent and independent variables:

The evaluation of these variables will be carried out in conjunction with the cardiology service of the IMED Valencia Hospital. At the Hospital IMED, tests related to the patient's risk stratification (ergospirometry, echocardiography and biochemical profile) will be performed, and at CEU Cardenal Herrera University the patient's respiratory and functional capacities will be evaluated (pressure measurement, incremental Shuttle test, evaluation of strength, functional parameters of the lower limb), in addition to quality of life and sexual dysfunction questionnaires.

All variables will be evaluated at 3 different times: pre-intervention, immediate post-intervention and one year follow-up.

- Cardiology Service (Hospital IMED Valencia):

- Cardiopulmonary exercise testing (CPET), evaluated by ergospirometry. The stress test with oxygen consumption consists of subjecting the patient to physical exercise with a controlled and progressive workload, taking measurements before, during, and after carrying out said work, and subsequently analyzing the data obtained . This test provides us with information about their cardiac, pulmonary, musculoskeletal function, and the response of all of them to physical exercise, constituting essential information for a correct evaluation of the patient's situation, establishment of a prognosis, and a good point of evaluation. Departure for the design of cardiac rehabilitation programs in the population after acute myocardial infarction. Among the necessary equipment, a cycle ergometer / treadmill is essential, as well as measurement and analysis equipment, such as a cardiopulmonary exercise tower, metabolic cart, electrocardiogram, pulse oximeter, blood pressure monitor, and additional equipment (resuscitation cart, stretcher of examination, oxygen bullet) and accessories^34^.
- Ejection Fraction, measured by echocardiography. Ejection fraction is defined as the stroke volume divided by the ventricular volume at the end of diastole. In the left ventricle, it usually has a value of about two-thirds (55 to 65%). In patients who have suffered an acute myocardial infarction, the ejection fraction serves as an indicator of risk, along with other elements. Thus, the patient's risk can be stratified into Low, Medium and High.

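### The pulmonary stenosis exclusion has its inequality reversed: it bars low gradients and does not itself bar high ones

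*Protocol*

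**What the plan says.** The Protocol, Participants section, has an exclusion item that lists pathologies in which exercise is contraindicated. Two of them are valve stenoses defined by a resting systolic gradient, one directly after the other:

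- Aortic: "gradient aortic stenosis resting systolic> 50mmHg"
- Pulmonary: "pulmonary stenosis with resting systolic gradient <50mmHg"

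Other entry criteria bear on the same patients. Inclusion requires acute coronary syndrome "with a Low or Medium risk stratification according to the stress tests performed by the cardiology service", and a medical prescription. The exclusions also cover "severe or moderate LV or RV dysfunction", baseline oxygen saturation below 90%, and abnormal exercise-test findings: "Alterations in ergospirometry: severe exercise-induced arrhythmias, ST depression with effort, exaggerated hypertensive response, hypotension on exertion and chest pain". Under Outcome measures, the tests behind the risk level are described ("risk stratification (ergospirometry, echocardiography and biochemical profile) will be performed"), with the remark that "the ejection fraction serves as an indicator of risk, along with other elements".

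The Introduction names two absolute contraindications to cardiac rehabilitation. One is dissecting aortic aneurysm and the other is "severe obstruction of the left ventricular outflow tract without surgical indication".

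**The concern.** A stenosis gradient rises as the valve narrows. In a list meant to keep out patients for whom exercise is unsafe, the limit should catch the high values. The aortic item does so. The pulmonary item uses the same limit with the opposite sign, so it catches the low values.

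This is a safety criterion, and a literal reading errs both ways. A patient with mild pulmonary stenosis is turned away without a clinical reason, and a patient with severe stenosis meets no gradient rule at all. A screener must either apply a reversed criterion or depart from the protocol, and anyone auditing eligibility would have to audit against the wrong text.

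**Working it through.** The protocol gives no figure to reproduce here. The check is a logical one, on the printed sign and its neighbours.

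**1. The two gradient items side by side** (Protocol, Participants, exclusion criteria)

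| Item | Limit | Excluded if gradient is | Side excluded |
|---|---|---|---|
| Aortic stenosis | 50 mmHg | above the limit | tighter stenosis |
| Pulmonary stenosis | 50 mmHg | below the limit | milder stenosis |

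Measure and limit are the same and the sign is opposite, so 1 of 2 items is reversed.

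**2. The other signs in the same sentence.** There are four: HTN above 40 mmHg, aortic gradient above 50 mmHg, systemic hypertension above the 95% percentile, and oxygen saturation below 90%. Each points to the harmful side. The saturation item shows that the less-than sign is used where a low value is the dangerous one. Only the pulmonary item points to the harmless side.

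**3. Literal test of the pulmonary item**

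| Gradient (mmHg) | As printed (exclude if < 50) | Sign reversed (exclude if > 50) |
|---|---|---|
| 20 | excluded | not excluded |
| 49 | excluded | not excluded |
| 50 | not excluded | not excluded |
| 80 | not excluded | excluded |

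Apart from the boundary value of 50, the two rules give opposite answers.

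**4. Does anything else replace the item?** The risk level, the medical prescription, the ventricular dysfunction exclusion, the saturation limit and the ergospirometry exclusions could each stop some patients with a high gradient. None states a pulmonary gradient limit. The sentence on contraindications in the Introduction supports the direction, since severe outflow obstruction is the contraindicated side. However, it concerns the left ventricle and sets no pulmonary limit.

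**5. What a wrongly admitted patient would undergo** (Protocol, Intervention: training program). The programme has 20 sessions, each with 20 minutes of aerobic and 20 minutes of strength work in the training phase:

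- Total: 20 × (20 + 20) = 20 × 40 = 800 minutes
- Aerobic: 20 × 20 = 400 minutes
- Strength: 20 × 20 = 400 minutes

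The session times are approximate, and the dose is the same in either arm. It is what every participant is prescribed, so it describes the exposure of such a patient and does not measure how often the error would occur.

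**The case against.** The strongest reply is that the slip is obvious and the harm remote. For harm to follow, a patient after an acute coronary syndrome must also have severe pulmonary stenosis, be rated low or medium risk by cardiology, and be given a prescription. The same patient must have no moderate or severe ventricular dysfunction, a saturation of at least 90% and an acceptable ergospirometry. A physician must then read a list of exercise contraindications as allowing an 80 mmHg gradient, although the list's heading and the aortic item beside it show the intent. Echocardiography is among the tests used for risk stratification, so such a stenosis might well be noticed.

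Much of this stands. Few patients, perhaps none, would be affected, and no statistical property of the trial changes. It does not make the printed criterion right. The protocol gives the pulmonary gradient its own item alongside all these safeguards, and none of them contains that limit.

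A second objection is that the Introduction is weak support. It does not name pulmonary stenosis among the absolute contraindications, and the outflow obstruction it does name is left-sided. That is fair: the argument rests on the heading of the list and the aortic item, and the Introduction only agrees in direction.

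A third is that the whole sentence is poorly rendered. The word order of the aortic item is scrambled, and the meaning of HTN above 40 mmHg is unclear. The working criteria used by the staff may therefore be correct, and an error in reading the PDF cannot be fully excluded. The documents cannot settle this, but a look at the source file can.

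**Conclusion.** The concern holds: the criterion is wrong as written. One of the two stenosis-gradient items is reversed, in an operative eligibility rule, and no other text in the protocol corrects it.

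The conclusion rests on two things: a higher gradient means a tighter stenosis, and the list is meant to exclude patients for whom exercise is unsafe. That a greater-than sign was intended is inferred from the heading and the aortic item; the protocol does not say so.

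The number of patients cannot be computed, because there is neither a prevalence nor a sample size to work from. That few are affected is an assumption. Both arms are screened by the same rule, so alpha, power and the comparison between the groups are untouched. The point should be fixed because it is a safety criterion and the correction costs almost nothing.

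**What to change.** Have the cardiology service confirm the intended limit. Then amend the exclusion criterion so that pulmonary stenosis is excluded when the resting systolic gradient is above 50 mmHg, in line with the aortic item. Check the sign against the source file and any screening form at the same time.

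The cost is one character in an eligibility amendment. No new measurement is needed, because the item as printed already requires the gradient to be known.
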